#### Missing values

3.4.1

Electronic data entry and follow up procedures will be used to minimise missing data. Attrition will be minimised through participant follow up including multiple attempts to re-contact though clinic visits, telephone, email and text. Missing values will be assessed to determine if they are random. If the missing data are found to be non-random, an intention-to-treat analysis will be conducted, and multiple imputation methods will be applied.

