### Statistical analysis

3.4

For the primary outcome variable (K10), a linear mixed effects regression model will be used to show any change, with participant identification number and study site as random effects. Age, gender, ethnicity, socio-economic status, type of diabetes, time and intervention group will be included as fixed effects. A significant interaction between intervention group and time (Baseline vs Follow Up) would indicate that the average change in K10 was significantly different between intervention and control groups [31]. This is the main test of the study and will be subjected to a significance level of α = 0.05. Level of significance will also be indicated using p-values. The effect sizes will be presented as the difference between the average decrease in K10 between intervention groups.

A linear mixed effects regression model will also be used for the secondary outcome variables including a change in; (1) HbA1c (2) PAID and (3) weight in kilograms. To account for multiple testing, a false discovery rate method such as the Benjamini-Hochberg procedure [32], will be adopted for the secondary outcome variables. The effect sizes will be presented as the difference between the average change in outcome between intervention groups. Results will be visualised using a forest plots. For all linear mixed effects models, model diagnostics will be conducted, including, but not limited to (a) examining the residuals for departures from normality, (b) collinearity between covariates using the variation inflation factor and (c) examination of outliers to see if they have too much influence on the results of the analysis. Consequential departures from normality and/or highly influential outliers will be handled using bootstrapping or through transformation of the outcome variable.

A generalised linear mixed effects regression model with a Poisson error model [33] will also be used for the secondary outcome variables; (4) the total number of hospital and/or emergency department admissions and (5) the total number of hospital and/or emergency department admissions due to diabetic keto-acidosis/hyperglycaemia. The models will be examined for over or under dispersion and a more appropriate error model will be adopted if necessary.

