Analyses will be adjusted for the following confounders: age, gender, ethnicity, socio-economic status (measured using postcode and Socio-Economic Indexes for Areas tool (SEIFA: Australian Bureau of Statistics), study site, and type of diabetes. The methods adopted will be the same for the primary (MHC) and nested exploratory (No-MHC) RCTs. If necessary, multiple imputation by chained equations [34] will be used to provide intention-to-treat results.

Interviews with participants and healthcare professionals will be conducted utilising the Reach, Effectiveness, Adoption, Implementation, and Maintenance (RE-AIM) framework to evaluate community and clinical impact [35]. The interviews will assess project engagement and implementation, effects of the app, and feedback and recommendations on app content and design. Interviews will be transcribed, coded to identify themes and sub-themes in NVivo and undergo reflexive thematic analysis to present key findings. Reflexive thematic analysis was chosen due to its high recommendation by leading qualitative researchers in the context of healthcare interventions with psychological impact and social outcomes [36]. Briefly, a 6-step process to analysis will involve: 1) data cleaning and familiarisation; 2) coding, where codes relate to features of the data that has been generated; 3) theme development through organisation of codes into broader themes across the dataset; 4) theme review and refinement; 5) theme naming and defining; and 6) reporting of findings.

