#### Sensitivity analysis

3.4.2

A per protocol analysis will be performed and compared with the results of the intention-to-treat analysis. For the per protocol analysis, only those participants considered to have received the Perx app will be included in the analysis. Participants will be considered to have used the Perx app if they have logged into the app and completed at least one task during the intervention period.

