#### Power calculations

3.4.3

Based on data published previously (behavioural intervention K10 change 21.2 ± 9.4 vs baseline 25.7 ± 9.7 Cohen d = 0.5), a sample size of 64 per group in the primary RCT will be required to identify a moderate effect size of 0.5 between intervention and control group, in a *t*-test model with power = 0.8, alpha 0.05. An additional 14 participants will be included to allow for an attrition rate of 10 % (total n = 142). The nested exploratory RCT (No MHC) is considered an exploratory study as it could not be powered.

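### Section 3.4.1 makes the intention-to-treat analysis and multiple imputation depend on finding the missing data non-random; this conflicts with section 3.4.2, and the term is undefined

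*Protocol article*

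**What the plan says.** Four parts of the protocol article bear on the point.

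- **Section 3.4.1, Missing values.** The rule starts with an assessment: "Missing values will be assessed to determine if they are random". It continues: "If the missing data are found to be non-random, an intention-to-treat analysis will be conducted, and multiple imputation methods will be applied". No definition of random, no test and no threshold is given, and no analysis is named for the opposite finding.
- **Section 3.4, Statistical analysis (imputation).** The method is named, again conditionally: "If necessary, multiple imputation by chained equations [34] will be used to provide intention-to-treat results".
- **Section 3.4.2, Sensitivity analysis.** Here ITT carries no condition: "A per protocol analysis will be performed and compared with the results of the intention-to-treat analysis". Per protocol is the only analysis described under this heading.
- **Section 3.4, Statistical analysis (primary model).** For K10, "a linear mixed effects regression model will be used to show any change, with participant identification number and study site as random effects". The group-by-time interaction is the test of interest: "This is the main test of the study and will be subjected to a significance level of α = 0.05". The text does not name the analysis set for this model, and it does not exclude participants without a 6-month value.

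**The concern.** ITT is a rule about who is analysed and in which arm. It follows from randomisation and holds whatever the reason for missing values. Section 3.4.1 instead makes it the consequence of a judgement reached after the data are in, with no stated criterion. As written, the population for the main K10 test could be settled after someone has looked at the pattern of loss.

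The second difficulty is the undefined trigger. Under one meaning of *non-random* it cannot be evaluated and the named remedy does not fit it. Under another it can be partly evaluated and the remedy does fit. A reader cannot tell which is meant.

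This matters because K10 is self-reported, participants know their allocation, and there is one post-baseline measurement, so a participant lost to follow-up contributes no outcome after baseline. The Discussion itself allows that loss may exceed the planned 10%.

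**Working it through.** **1. The plan's own figures.** Section 3.4.3 gives K10 means of 25.7 (SD 9.7) and 21.2 (SD 9.4), a difference of 25.7 − 21.2 = 4.5 points. The pooled SD is √((9.4² + 9.7²)/2) = √91.2 = 9.55, so d = 4.5/9.55 = 0.47, which the plan rounds to 0.5. With d = 0.5, "power = 0.8, alpha 0.05" and a two-sided t-test (sidedness is assumed), the requirement is 63.8, hence 64 per group. Then 128 + 14 = 142. The sample size reproduces and is not at issue; the 4.5 points serve below only as a yardstick.

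**2. The sections side by side.**

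| Section | Status of ITT | Status of imputation |
|---|---|---|
| 3.4 | the result that imputation serves to provide | if necessary |
| 3.4.1 | follows from a non-random finding | follows from the same finding |
| 3.4.2 | exists, without condition | not mentioned |

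If missingness is judged random, section 3.4.1 names no ITT analysis, yet section 3.4.2 needs one as the comparator for per protocol. The wording in 3.4.1 has to change for the two to agree.

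**3. The two meanings of *non-random*.**

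- *MNAR*: loss depends on the unseen 6-month K10, given what was observed. Observed data cannot show this. Standard chained-equation imputation assumes MAR, so it does not correct the problem that triggered it.
- *Not MCAR*: loss may depend on observed variables such as baseline K10 or site. This can be partly checked, and MAR-based imputation is suitable.

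Under both meanings, making ITT conditional is wrong.

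**4. Does MAR imputation behave as step 3 says?** A simulation used 71 per arm, a true effect of −4.5, SD 9.5 and 1,500 replicates, with regression imputation of 6-month K10 within arm. Assumptions not in the article: baseline to follow-up correlation 0.5, and log-odds of dropout in the app arm rising by 1 per SD of baseline K10 (MAR) or of 6-month K10 (MNAR). Bias after imputation:

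| Overall attrition | MAR dropout | MNAR dropout |
|---|---|---|
| 10% | −0.03 | −0.77 (0.77/4.5 = 17%) |
| 20% | −0.06 | −1.35 (30%) |
| 30% | +0.05 | −1.91 (42%) |

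The Monte Carlo standard error is about 0.04 to 0.05, so there is essentially no bias under MAR. Under MNAR the benefit is exaggerated. The size depends on the assumed mechanism.

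**5. A simpler illustration of MNAR bias.** Suppose lost participants are δ points worse at 6 months than a MAR model predicts, equally in both arms. The bias towards the app is (p_app − p_control) × δ. With δ = 5 (assumed):

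- 10% lost in each arm: (0.10 − 0.10) × 5 = 0
- 20% versus 10%: (0.20 − 0.10) × 5 = 0.5 points; 0.5/4.5 = 11%
- 20% versus 5%: (0.20 − 0.05) × 5 = 0.75 points; 0.75/4.5 = 17%

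With SD about 9.5 and 64 per arm, the unadjusted standard error is 9.5 × √(2/64) = 1.68, so 0.5 points is about 0.3 standard errors.

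If instead only app-arm dropouts are 4.5 points worse, an estimate of −4.5 becomes −4.5 + 0.10 × 4.5 = −4.05, −4.5 + 0.20 × 4.5 = −3.60 and −4.5 + 0.30 × 4.5 = −3.15 at 10%, 20% and 30% app-arm loss.

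**The case against.** The strongest reply is that, read as a whole, the article intends ITT throughout. Section 3.4.1 says if, not only if; section 3.4.2 presumes an ITT result; and section 3.4 makes imputation, not ITT, the conditional step. This stands as far as intent goes. A reader might infer from 3.4.1 that there is no ITT analysis when data are judged random, and the article as a whole does not support that. It does show that the condition in 3.4.1 is out of place.

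A reader might also infer that imputation is invoked exactly when its assumption fails. That holds only if *non-random* means MNAR, which the article does not say.

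Third, the primary model limits the harm. Fitted to every randomised participant with any K10 value, the mixed model is valid under MAR without imputation, and the article states no exclusion that would prevent this. So the primary analysis is not left unprotected against MAR loss. What is missing is a plain statement that all randomised participants enter the model.

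Fourth, the bias figures are not the effect of the conditional rule. A MAR mixed model fitted to everyone would carry the same bias, and only a sensitivity analysis would display it. The inputs are assumed, and 20% versus 10% loss averages 15%, above the planned 10%. The article also does not say that more distressed participants are likelier to be lost; it mentions poor attendance and uncertain responsiveness.

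Finally, details of an MNAR sensitivity analysis are commonly left to an analysis plan, which is not shown. Their absence is not the finding. The finding is a published rule that is wrong as stated.

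**Conclusion.** The point holds as an error and inconsistency in a stated rule. Section 3.4.1 conditions ITT on a post-hoc and undefined finding, while section 3.4.2 requires ITT regardless. Conditioning ITT on the missingness mechanism is wrong under either meaning of *non-random*; the mismatch between trigger and remedy arises only under the MNAR meaning.

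No number measures the effect of the rule itself. The figures of 0 to 0.75 K10 points, and the larger simulated biases, are generic illustrations of MNAR bias on assumed inputs. They show why a sensitivity analysis is worth running, not what the wording costs. Because the planned mixed model is already suitable under MAR if fitted to all randomised participants, this should be fixed but does not undermine the trial.

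**What to change.** Replace the rule in section 3.4.1, and align sections 3.4 and 3.4.2 with it:

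1. State that the primary analysis is ITT: all randomised participants, by allocated arm, whatever the pattern of missing data. Use the section 3.4 mixed model under MAR on all available K10 values, or multiple imputation under MAR.
2. Delete the missingness finding as a trigger. Missingness can still be described by arm and baseline characteristics. If the word random is kept, say whether MCAR or MAR is meant.
3. Run a delta-adjusted sensitivity analysis of 6-month K10 regardless of that description. For example, shift imputed values by 0 to +5 points, in the app arm alone and in both arms, and report the shift at which the conclusion changes.

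The cost is revised wording and a few extra imputation runs. Sample size, data collection and trial conduct do not change.

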#### Sensitivity analysis

3.4.2

A per protocol analysis will be performed and compared with the results of the intention-to-treat analysis. For the per protocol analysis, only those participants considered to have received the Perx app will be included in the analysis. Participants will be considered to have used the Perx app if they have logged into the app and completed at least one task during the intervention period.

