##### Randomisation and blinding

3.3.2.5

Randomisation to either “app” or “no app” within each study (MHC and No MHC) will be allocated by the database randomiser using randomisation by minimisation stratified within site. Allocation will not be concealed from participants or healthcare workers, however research staff collecting data will be blinded at baseline and follow-up. Participants assigned to the intervention arms will be onboarded to the Health Hub within the Perx app appropriate to their diabetes type. Participants will be invited to onboard via email and text message notifications (SMS) from Perx Health, which will include instructions on how to download the app and sign in on their smartphones. Research Assistants collecting data and the study statistician will be blinded to a participant's randomisation status. Allocation to the app will not be concealed from participants or healthcare workers.

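### The per-protocol rule in Section 3.4.2, read literally, excludes every control; if controls are kept, it compares self-selected app users with all controls, a contrast randomisation does not protect

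*Protocol article*

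**What the plan says.** Section 3.4.2 (Sensitivity analysis) of the protocol article contains one analysis. Its purpose is a comparison with ITT: "A per protocol analysis will be performed and compared with the results of the intention-to-treat analysis". Its inclusion rule is that "only those participants considered to have received the Perx app will be included in the analysis". Use is then defined by behaviour during follow-up: "Participants will be considered to have used the Perx app if they have logged into the app and completed at least one task" in the intervention period. The section moves from having received the app to having used it without separating the two, and gives no rule for controls.

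Section 3.3.2.5 (Randomisation and blinding) says who gets the app: "Participants assigned to the intervention arms will be onboarded to the Health Hub within the Perx app appropriate to their diabetes type". The other arm is allocated to no app.

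Section 3.4 (Statistical analysis) defines the effect as a contrast between arms: "A significant interaction between intervention group and time (Baseline vs Follow Up) would indicate that the average change in K10 was significantly different" across the two arms. It names the adjustment set: "Analyses will be adjusted for the following confounders: age, gender, ethnicity, socio-economic status", with study site and type of diabetes. It applies the same methods to the primary trial (mental health condition, MHC) and the nested exploratory trial (No-MHC).

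**The concern.** There are two layers.

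First, the rule and the purpose of the analysis do not fit together. A set made up only of people who received the app contains one arm. A group-by-time interaction cannot be estimated from one arm, so there is nothing to compare with the ITT estimate. What remains is a before-after change in app users. That would be hard to interpret in this trial. Many participants enter the primary RCT because of a high K10 or PAID score at screening (Section 3.3.2.4), so some fall in K10 by regression to the mean is possible, and everyone also receives an activity tracker and access to peer support (Section 3.3.2.6).

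Second, the obvious repair has its own weakness. If all controls are kept and only app non-users are dropped, the app arm is filtered on engagement after randomisation and the control arm is not. The listed covariates are demographics, site and diabetes type, and none is aimed at self-selection into app use.

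At stake is whether the only check in Section 3.4.2 can do its job. A reader who sees it agree or disagree with ITT could not tell an app effect from a selection effect.

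**Working it through.** **Step 1. Set the passages side by side.**
- Inclusion (Section 3.4.2): received the app.
- Who can receive it (Section 3.3.2.5): intervention arms only.
- Controls who meet the rule as written: 0.
- Effect to be compared (Sections 3.4 and 3.4.2): difference between arms in change. Not estimable with 0 controls.

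Nothing elsewhere in the article restores controls to this set.

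**Step 2. The plan's own figures, for scale.** Section 3.4.3 gives d = 0.5, power 0.8 and alpha 0.05. A two-sided two-sample t-test needs 63.77, so 64 per group, as stated. The cited K10 SDs of 9.4 and 9.7 give √[(9.4² + 9.7²)/2] = 9.55, and (25.7 − 21.2)/9.55 = 0.47, which the plan rounds to 0.5. The point does not depend on these figures; they only supply a scale.

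**Step 3. Illustrative bias if controls are kept and non-users dropped, with no true app effect.** Let u be the share of the app arm that meets the one-task rule, and ρ the correlation between a normally distributed engagement trait and improvement. Neither is in the article; both are assumed. Users are the top fraction u on that trait, so their mean improvement differs from that of their whole arm, and hence from that of controls, by

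bias (in SDs of improvement) = ρ × φ(z)/u, with z = Φ⁻¹(1 − u).

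| u | φ(z) | φ(z)/u | ρ = 0.2 | ρ = 0.3 |
|---|---|---|---|---|
| 0.6 | 0.386 | 0.644 | 0.13 | 0.19 |
| 0.7 | 0.348 | 0.497 | 0.10 | 0.15 |
| 0.8 | 0.280 | 0.350 | 0.07 | 0.10 |
| 0.9 | 0.175 | 0.195 | 0.04 | 0.06 |

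The range is 0.04 to 0.19 SD. A negative ρ reverses the sign.

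**Step 4. A second parameterisation, in K10 points.** Let D be the difference in K10 change between users and non-users that the app does not cause (assumed). Then bias = (1 − u) × D. The setting is 64 evaluable controls, 64u users and SD 9.55.

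| u | D | Bias (K10 points) | Two-sided false-positive rate |
|---|---|---|---|
| 0.5 | 2 | 1.0 | 7.7% |
| 0.5 | 4 | 2.0 | 16.2% |
| 0.7 | 4 | 1.2 | 9.9% |
| 0.9 | 2 | 0.2 | 5.2% |
| 0.9 | 4 | 0.4 | 5.6% |

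Dropping non-users also costs precision: power for d = 0.5 is 63% at u = 0.5 and 78% at u = 0.9.

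Both tables are unadjusted. The SD of 9.55 is for K10 scores rather than change, so the SD units of Step 3 and the plan's d are not on an established common scale.

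**The case against.** The strongest reply is that the zero-control reading is not what the authors meant. The sentence just before the rule promises a comparison with ITT, which needs both arms, so the rule most likely says who in the app arm counts as treated. That is fair as to intent. A reader might infer that the sponsor plans a single-arm analysis, and the document does not support that. What stands is that the rule uses the word only, says nothing about controls, and would exclude them all if followed.

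A second reply is that conditioning on adherence is a known limit of every per-protocol set, that this one is labelled a sensitivity analysis, and that the main test does not use it. This also stands, and it limits the severity. It does not make the contrast a sound check on ITT.

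A third reply is that the size is pure assumption. The threshold is a login plus one task over six months, with in-app communications every four to five days or so (Section 3.3.1). If most of the app arm meets it, the bias sits near the bottom of the range. That is correct, and the figures above are illustrations only.

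A reader might also infer that the bias must favour the app because engaged participants do better. The article does not show this. More distressed participants might engage more, or less distressed users might have less room to improve on K10.

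Finally, a complier average causal effect is not free of assumptions. Under one-sided non-compliance it is roughly the ITT estimate divided by uptake, so its test largely repeats the ITT test. Its exclusion restriction is open to doubt here: someone who completes no task may still have received messages or browsed resources, allocation is not concealed from participants, and K10 is self-reported. These cautions belong in the fix.

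**Conclusion.** The point holds for the sensitivity analysis. As written, the inclusion rule leaves no controls and cannot deliver the planned comparison with ITT. On the likely intended reading, the comparison is between self-selected users and all controls, is not protected by randomisation, and could err in either direction.

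The size is unknown. The 0.04–0.19 SD range rests wholly on assumed uptake of 60–90% and an assumed correlation of 0.2–0.3. The 0.2–2.0 K10-point range rests on assumed uptake of 50–90% and an assumed difference of 2–4 points. It would be tempting to read the top figure as a large share of the d = 0.5 design effect, but that takes the worst pair of assumptions and mixes two SD scales, so it should not be quoted that way.

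Both trials are affected, because the same methods apply to each. The primary test and the sample size are untouched. The issue is minor to moderate.

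**What to change.** Rewrite the inclusion sentence in Section 3.4.2 so that it:
- states that all randomised controls are retained;
- uses one term, either received or used, with the login-plus-one-task definition attached to it.

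Then estimate the effect among app users as a complier average causal effect. Use everyone randomised in both arms, with allocation as the instrument and a complier defined by the existing one-task rule. Controls are not given the app, so non-compliance is one-sided. Report the estimate beside ITT. State the exclusion restriction, and say that messages and browsing may affect participants who complete no task. If the simple per-protocol comparison is also kept, label it a non-randomised comparison.

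The cost is one paragraph of wording and one further model. The app-use and task data are already to be captured (Section 3.4.4). The interval will be wider than for ITT by about 1/u: 1.11 times at 90% uptake, 1.25 at 80% and 1.67 at 60%. Reporting observed uptake by trial would let readers judge how much the issue matters.
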